## Results

Participant recruitment took place between March 2023 to April 2023. In all, 30 participants were eligible and completed the study. Upon selection of these patients and completion of the 3-week research period, a statistical analysis was conducted on the variability of capillary blood glucose levels during the first and third weeks. Subsequently, these data were used to determine the required sample size (n) necessary to draw valid conclusions regarding the proposed research objectives. Furthermore, in addition to the capillary blood glucose values, the data types presented in Table 1 will be scrutinized to ensure the absence of statistical discrepancies between groups 1 and 2. The study was approved by the Brazilian Registry of Clinical Trials (RBR-6wg54rb) on March 7, 2023. Figure 2 shows a sample table of how the results will be presented.

**Table 1 table1:** Epidemiological, clinical, and laboratory data (n=30).

Characteristics	Values
Participants	n
Age (years)	Mean or median
Sex (female)	n, %
Insulin users	n, %
BMI (kg/m^2^)	Mean or median
Abdominal circumference (cm)	Mean or median
Duration of diabetes (years)	Mean or median
STOP-Bang^a^ (score)	Mean or median
Glycohemoglobin (%)	Mean or median

^a^STOP-Bang: snoring, tiredness, observed apnea, high blood pressure, BMI, age, neck circumference, gender.

**Figure 2 figure2:**
[figure not shown]
Sample table showing how results will be reported. Unpaired-sample *t* tests or Wilcoxon tests will be used.

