### Glycemic Variability and Crossover Studies

Crossover studies present an advantage over parallel group studies: comparing 2 or more interventions in the same individual reduces possible biases related to differences between groups. Such a design is suitable for chronic diseases and for testing drugs that control a disease but do not cure it. Curing a disease in one period of the study would make it meaningless to use another drug or even a placebo in the following period. When studying an outcome that is influenced by several variables, this design allows for a more reliable comparison with a smaller sample. This is the case for assessing glycemic variability in patients with T2DM. Glycemic variability in patients with T2DM can be influenced by several factors, including medications, duration of diabetes, age, diet, and physical activity. In the evolution of the treatment of diabetes mellitus, there has been an effort to develop drugs that reduce variability in glycemia: dipeptidyl peptidase 4 (DPP-4) inhibitors, GLP1 (glucagon-like peptide 1) analogues, and ultra-slow insulins. Patients with T2DM are treated with a diverse combination of the available drugs. For this reason, pairing groups for a comparison of glycemic variability would be a complex task. Added to this are individual differences in diet and physical activity. Thus, a crossover study is more suitable for the purpose of this work.

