### Statistical Analysis

If quantitative variables adhere to a normal distribution, as represented by the Gaussian curve, their central tendency will be expressed as mean and their dispersion will be quantified by the SD. If the distribution of these variables does not follow a normal distribution, then their central tendency will be described by the median and their dispersion will be characterized by the 25% and 75% quartiles. The Shapiro-Wilk test will be used to assess normality. Categorical variables will be presented using both absolute frequencies and percentages.

Statistical analyses of normal quantitative variables, both before and after the intervention, will be conducted using a paired 1-tailed *t* test. When the distribution is not normal, the Wilcoxon test will be used. The study will have 2 intervention tails: placebo-washout-melatonin and melatonin-washout-placebo. Comparison of blood glucose levels will be performed between the time when the patients used melatonin and the time they used placebo.

The patients will be compared with one another based on the capillary blood glucose results obtained during the first and third weeks.

The epidemiological, clinical, and laboratory data of the patients will be compared between groups 1 and 2 in order to evaluate whether the randomization process has generated groups that lack statistical differences that may influence the research results.

The significance level will be .05 and the software of choice will be SPSS (version 20.0; IBM Corp).

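### The Figure 2 caption attaches unpaired t tests to the results table, contradicting the paired test in the Statistical Analysis section and the within-patient rationale for the crossover

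*Protocol article*

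**What the plan says.** The Statistical Analysis section states that analyses of normal quantitative variables "will be conducted using a paired 1-tailed *t* test". For other data it adds: "When the distribution is not normal, the Wilcoxon test will be used". It does not say which Wilcoxon test. The same section says the comparison of glucose levels will be "performed between the time when the patients used melatonin and the time they used placebo", so the contrast of interest lies between two periods in the same people.

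The Methods section on glycemic variability and crossover studies gives the reason for the design: "comparing 2 or more interventions in the same individual reduces possible biases related to differences between groups". It adds that for an outcome influenced by several variables "this design allows for a more reliable comparison with a smaller sample".

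The Results section introduces the planned display: "Figure 2 shows a sample table of how the results will be presented". The caption of that figure then states: "Unpaired-sample *t* tests or Wilcoxon tests will be used".

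**The concern.** The article names two incompatible t tests, and the unpaired one sits under the table meant to show the results. Baseline characteristics have their own display, Table 1. The caption also follows the same pattern as the Statistical Analysis section (a t test, or Wilcoxon), so the treatment comparison is its most natural subject.

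An unpaired test on the melatonin and placebo values would treat each patient's two weeks as coming from different people. That ignores their correlation, which is the source of the crossover's efficiency, and uses the wrong standard error. An effect that the planned paired analysis would probably detect could then be reported as null.

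Two other wordings leave the matter open. Wilcoxon is not identified as the signed-rank test, and next to the word unpaired it can be read as the rank-sum test. The Statistical Analysis section also has a loose sentence about comparing patients with each other on their week 1 and week 3 readings, which can be read as a between-patient comparison.

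**Working it through.** **Inputs from the article.** 30 patients, each measured in both periods, and a threshold of 30 for recruiting more (Sample Size); significance level .05, with a one-tailed paired t test (Statistical Analysis). The 30 is a pretest convention with no effect size, SD or power behind it, so there is no sample-size calculation to reproduce.

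**Assumptions.** Equal SD (sigma) in both periods, normal values, and within-patient correlation rho from 0 to 0.8. The article gives no rho.

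**Step 1: standard error of the mean difference.** The correct paired value is sigma × sqrt(2(1 − rho)/n). The unpaired value is sigma × sqrt(2/n). Their ratio is 1/sqrt(1 − rho). At rho = 0.5, for example, it is 1/sqrt(0.5) = 1.41.

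**Step 2: power and type I error at n = 30.** Paired power comes from the noncentral t distribution with 29 df and noncentrality d × sqrt(30)/sqrt(2(1 − rho)), where d is the difference in SD units. For each rho, d was set to give 80% paired power. The unpaired t test (58 df) was then applied to the same correlated data by simulation, with 200,000 replicates, one-sided at .05.

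| rho | d for 80% paired power | SE ratio | Unpaired power | Unpaired type I error |
|---|---|---|---|---|
| 0 | 0.658 | 1.00 | 81% | 5.0% |
| 0.3 | 0.550 | 1.20 | 71% | 2.5% |
| 0.5 | 0.465 | 1.41 | 58% | 1.1% |
| 0.7 | 0.360 | 1.83 | 32% | 0.2% |
| 0.8 | 0.294 | 2.24 | 14% | 0.03% |

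At rho = 0 nothing is lost. The unpaired test is marginally ahead there because it has more degrees of freedom.

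**Step 3: possible effect on the sample-size recalculation.** Assume a difference of 0.5 SD, 80% power and one-sided .05. The squared term is ((1.645 + 0.842)/0.5)² ≈ 24.7.

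- Paired: n = 2(1 − rho) × 24.7, which rounds up to 35, 25 and 15 patients at rho = 0.3, 0.5 and 0.7.
- Unpaired: n = 2 × 24.7, which rounds up to 50 values per treatment at any rho. In a crossover that is 50 patients.

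At rho = 0.5 the paired formula gives 25, below 30, so the study would be concluded. The unpaired formula gives 50, so more patients would be recruited. At rho = 0.3 both exceed 30, but the targets differ (35 against 50).

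**The case against.** The strongest reply is that the Methods already name the right kind of test. The Statistical Analysis section says paired, the Study Design section compares the placebo and melatonin periods, and the design rationale is within-patient. The only contrary statement of the test is one caption under a sample table, and a slip for paired is a likely explanation. This stands as a reason not to assume that the unpaired test will be used. It does not remove the conflict, because the reader cannot tell a slip from an intention.

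A second reply is that the caption may concern groups 1 and 2. The Statistical Analysis section plans to compare those groups and names no test for it, and the sentences leading to Figure 2 discuss the same comparison. An unpaired test is ordinary for that purpose. It would also be valid for comparing within-patient period differences between sequences, or for a week-1-only comparison of the groups. With the figure body not shown, such a use cannot be excluded. The caption, however, does not limit itself to it.

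Three stronger readings are tempting but unsupported:

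- A reader might infer that the primary comparison will be analysed unpaired. The article does not establish this.
- A reader might infer a large loss of power in any case. That depends on rho, which is unknown: the loss is nil at 0 and modest at 0.3. The article's argument that variability depends on medication, diabetes duration and age makes a positive rho plausible, but does not show how large it is.
- A reader might infer false-positive inflation, or a plan to choose the test after seeing the data. With positive rho the unpaired test is conservative. Nothing in the article shows an intent to choose, and its statisticians are to stay blind to bottle identity until the analysis is complete.

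**Conclusion.** The contradiction is real, and as written the caption attaches an unpaired test to the results. Because it concerns the test for the main comparison, it should be corrected, although the Methods already contain a suitable paired alternative.

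The consequence is conditional: it arises only if the caption's test is applied to melatonin and placebo values from the same patients. The standard error is then overstated by about 1/sqrt(1 − rho). A comparison with 80% paired power would keep between about 81% (rho = 0) and 14% (rho = 0.8), and intervals would be too wide whenever rho is positive. These figures rest on assumed correlations, equal SDs and normal data.

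The sample-size recalculation would be affected only if it too followed the unpaired test. The 25-against-50 contrast is an illustration at an assumed 0.5 SD and rho = 0.5, not an estimate for this trial.

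**What to change.** Bring the Figure 2 caption into line with the Statistical Analysis section. For every melatonin-versus-placebo comparison, state the paired t test, or the Wilcoxon signed-rank test where the data are not normal, and name the signed-rank test in the Statistical Analysis section as well. Limit unpaired tests to comparisons between groups 1 and 2, such as baseline data, and say so. Confirm that the sample-size recalculation uses the SD of the within-patient differences.

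The cost is one caption and a few words in the Statistical Analysis section. No change to the design or to data collection is needed.

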## Discussion

### Anticipated Findings

The role of melatonin in the glycemic control of T2DM patients has been studied for a number of years [25]. However, studies on the role of melatonin in glycemic variability are not available. Our work does not aim to assess the impact of melatonin on glycohemoglobin levels, but rather its effect on glycemic variability. The hypothesis was tested based on the fact that melatonin, as a hormone, plays a crucial role in regulating circadian rhythms. This notion is logical to us, given that a hormone whose secretion is primarily nocturnal, such as melatonin, governs numerous biological rhythms [26]. Our findings could signify a great advance in the management of T2DM, as it would provide a new therapeutic target: deficient melatonin production in affected individuals. The primary aim of this work is present a new approach toward managing and preventing chronic complications in patients diagnosed with T2DM.

### Limitations

The limitations inherent in this study pertain to an analysis of glycemic variability conducted over a short span: only a few days after intake of melatonin or placebo. The effectiveness of melatonin in reducing glycemic variability might occur with longer use.

A second limitation of this study is derived from the fact that endogenous melatonin peaks in the middle of the night. The exogenous melatonin administered to patients in this study will not reproduce the physiological rhythm of endogenous melatonin.

A third limitation is the fact that patients may have diet and physical activity fluctuations between weeks 1 and 3 of the study, despite the guidance given initially, which might interfere with glycemic variability.

A fourth limitation of this study is the fact that we will not assess the prevalence of the *MTNR1B* mutation, which can determine a poorer glycemic response to melatonin use.

### Conclusions

The study of glycemic variability in patients with T2DM is fundamental for the prevention of chronic complications of the disease. Melatonin is a substance involved in biological rhythms, including those related to glucose control, such as insulin secretion. The existing knowledge that patients with T2DM produce a smaller amount of melatonin motivated us to test the replacement of this hormone as an instrument for greater glycemic stability. As glycemic variability is influenced by several variables, we conclude that a crossover design will be more suitable than a paired-group design for this study to evaluate the role of melatonin in glycemic stability.

## Abbreviations

DPP 4: dipeptidyl peptidase 4
GLP1: glucagon-like peptide-1
MODD: mean of daily differences
STOP-Bang: snoring, tiredness, observed apnea, high blood pressure, BMI, age, neck circumference, gender
T2DM: type 2 diabetes mellitus
